## Abstract

**Background:**

Poor-grade aneurysmal subarachnoid hemorrhage (SAH) is associated with poor neurological outcome and high mortality. A major factor influencing morbidity and mortality is brain swelling in the acute phase. Decompressive craniectomy (DC) is currently used as an option in order to reduce intractably elevated intracranial pressure (ICP). However, execution and optimal timing of DC remain unclear.

**Methods:**

PICASSO resembles a multicentric, prospective, 1:1 randomized standard treatment-controlled trial which analyzes whether primary DC (pDC) performed within 24 h combined with the best medical treatment in patients with poor-grade SAH reduces mortality and severe disability in comparison to best medical treatment alone and secondary craniectomy as ultima ratio therapy for elevated ICP. Consecutive patients presenting with poor-grade SAH, defined as grade 4–5 according to the World Federation of Neurosurgical Societies (WFNS), will be screened for eligibility. Two hundred sixteen patients will be randomized to receive either pDC additional to best medical treatment or best medical treatment alone. The primary outcome is the clinical outcome according to the modified Rankin Scale (mRS) at 12 months, which is dichotomized to favorable (mRS 0–4) and unfavorable (mRS 5–6). Secondary outcomes include morbidity and mortality, time to death, length of intensive care unit (ICU) stay and hospital stay, quality of life, rate of secondary DC due to intractably elevated ICP, effect of size of DC on outcome, use of duraplasty, and complications of DC.

**Discussion:**

This multicenter trial aims to generate the first confirmatory data in a controlled randomized fashion that pDC improves the outcome in a clinically relevant endpoint in poor-grade SAH patients.

**Trial registration:**

DRKS DRKS00017650. Registered on 09 June 2019.

**Supplementary Information:**

The online version contains supplementary material available at 10.1186/s13063-022-06969-4.

## Administrative information

Note: the numbers in curly brackets in this protocol refer to SPIRIT checklist item numbers. The order of the items has been modified to group similar items (see http://www.equator-network.org/reporting-guidelines/spirit-2013-statement-defining-standard-protocol-items-for-clinical-trials/).

## Introduction

### Background and rationale {6a}

Poor-grade aneurysmal subarachnoid hemorrhage (SAH), defined as grades 4 and 5 according to the World Federation of Neurosurgical Societies (WFNS) [1], is associated with poor neurological outcome and high mortality [2–5].

The rupture of an intracranial aneurysm can cause brain swelling primarily due to severe damage of brain tissue and secondarily due to vasospasm followed by infarction that both leads to elevation of intracranial pressure (ICP). Studies have shown that brain swelling and elevated ICP are known to worsen outcomes following SAH [6–8]. Despite this, significant predictors of unfavorable outcomes in patients with poor-grade SAH are patient age, WFNS grade 5, signs of cerebral herniation, aneurysm size, and space-occupying hematoma [9].

Decompressive craniectomy (DC) is a well-established surgical intervention aiming to reduce increased ICP. After traumatic brain injury (TBI) and space-occupying stroke, DC has been shown to successfully reduce elevated ICP and also improve patient’s outcome in those strokes [10–13].

Besides a proven lifesaving effect in general, it is still debatable if an early decompression within 24 h after SAH—i.e., primary DC (pDC)—provides a better long-term functional outcome with lower rates of severe disability and dependency rates of patients or leads to a higher number of survival with dependent patients. A retrospective series of patients treated with a pDC in poor-grade SAH indicates that a pDC may be warranted in this severely ill subset of patients [14]. However, despite these promising data, there are no data from randomized controlled trials proving or disproving the beneficial effect of pDC, a rather aggressive surgical treatment compared to a neuro-intensive medical therapy with a secondary DC only performed if ICP cannot be handled by other treatment options [15–34].

Thus, we aim to investigate the effect of pDC in a prospective randomized trial regarding the mortality rate and the degree of disability of these patients.

### Objectives {7}

Comparison of the combination of mortality and severe disability between study arms, assessed by the modified Rankin Scale [35] (mRS) between both study arms 12 months after the subarachnoid hemorrhage, dichotomized in “favourable” (mRS 0–4) and “unfavourable” (mRS 5–6) outcome.

### Trial design {8}

PICASSO resembles a multicentric, prospective, 1:1 randomized, standard treatment-controlled, superiority study with blinded ratings with regard to the mRS assessment during telephone interviews. It will follow the recommendation and suggestion of CONSORT 2010 (Consolidated Standards of Reporting Trials). All patients included in the study will initially receive standard treatment according to the institutional guidelines of each participating site [4]. In the experimental arm, patients will undergo a pDC of at least 12 cm within the first 24 h after ictus. In the control arm, patients may undergo a secondary DC as ultima ratio therapy for therapy-refractory increased intracranial pressure (Fig. 1).

**Fig. 1 Fig1:**
[figure not shown]
Trial logo

## Methods: participants, interventions, and outcomes

### Study setting {9}

The trial will be conducted in 9 centers in Germany which must meet the structural and personnel requirements for performing the planned regular trial-related investigations (Fig. 2).

**Fig. 2 Fig2:**
[figure not shown]
Participating sites in Germany

### Eligibility criteria {10}

#### Inclusion criteria

Male or female subjects, aged ≥ 18 years and ≤ 80 yearsAneurysmal subarachnoid hemorrhageWFNS grades 4 or 5 at admissionDC can be performed within the first 24 h after symptoms of hemorrhage have started

#### Exclusion criteria

Moribund patient (mRS ≥ 4 before subarachnoid hemorrhage) due to other illnessesSAH due to any other cause than aneurysm rupture (e.g., traumatic, arteriovenous malformation (AVM), fistula, dissection)Patients with foreseeable difficulties to perform the follow-up adequatelyAny condition that, in the judgment of the investigator, could impose hazards to the patient if study therapy is initiated or affect the participation of the patient in the studyPatients with obvious evidence of irreparable brainstem or thalamic injury

### Who will take informed consent? {26a}

As determined by the inclusion criteria, patients that are eligible for the trial will be in a reduced state of consciousness and therefore unable to give informed consent. To protect the vulnerable patient population treated within the trial, we will perform the inclusion of the patients as regularly done for patients unable to give consent. This will include a second opinion of an independent physician before inclusion of a patient as well as informed consent by the legal representative of the trial participants and the informed consent by the patient himself in case of an improved mental state.

### Additional consent provisions for collection and use of participant data and biological specimens {26b}

Information on the collection and use of participant data will be integrated into the informed consent sheet.

## Interventions

### Explanation for the choice of comparators {6b}

Besides the aneurysm treatment in order to prevent re-bleeding and the administration of oral nimodipine as well as intensive care unit (ICU) observation and therapy, there is no causal/outcome-improving therapy available by now. The control group receives therefore the best medical treatment following actual guidelines as stated above. The control group will not be harmed in order to the randomization. Patients in the control group may undergo a secondary DC for therapy-refractory increased intracranial pressure. The experimental group will receive the best medical treatment as well as the pDC.

### Intervention description {11a}

#### Experimental group

All patients in the study arm will undergo a pDC of at least 12 cm combined with the best possible neuro-intensive medical therapy according to the international guidelines. pDC has to be performed within 24h after ictus.

#### Control group

Patients will receive the best possible neuro-intensive medical therapy according to the international guidelines. It may include a secondary DC as ultima ratio therapy for reducing increased intracranial pressure.

### Criteria for discontinuing or modifying allocated interventions {11b}

Subjects may withdraw from the trial at any time at their own request without stating the reason(s) for withdrawal. They will experience no disadvantage as a result of this decision and no alternative therapy will be withheld by the investigator.

Moreover, subjects may also be withdrawn at any time at the discretion of the investigator for safety, behavioral, or administrative reasons, e.g.:Medically indicatedContinuation is unacceptable because the risks outweigh the benefitsLack of compliance of the subjectSignificant protocol violationsLogistical reasons (e.g., subject changes his/her doctor or hospital or moves to another location)

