### Strategies to improve adherence to interventions {11c}

Not applicable, as interventions are performed early after poor-grade SAH while patients are unconscious.

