### Plans to promote participant retention and complete follow-up {18b}

Contact data (e.g., address, phone numbers) for each participant and their next of kin (if allowed) will be obtained after recruitment to ensure complete follow-up. We will reschedule phone calls if the participant requests this. Most of the other data (e.g., vital parameters, length of ICU stay, etc.) will be provided by the hospital information system collected in accordance with the indispensable (ICU) treatment.

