## Statistical methods

### Statistical methods for primary and secondary outcomes {20a}

Statistical analysis will be performed at the Institute of Medical Biometry, Informatics and Epidemiology (IMBIE) at the University of Bonn Medical Center. The rate of a favorable outcome will be compared between the treatment groups with a two-sided Mantel-Hanzel test at a level of 5%, stratifying for centers. The overall effect of therapy will be assessed by the calculation of a Mantel-Hanzel overall odds ratio with 95% confidence limits. For this analysis, the outcome of all patients with missing data for the primary outcome at 12 months will be counted as unfavorable.

This analysis will be repeated based on the PP population. Relevant differences between the results of ITT and PP analysis have to be critically discussed.

Mortality will be analyzed by calculating Kaplan-Meier estimators for survival in both treatment groups. Mortality after 7 and 90 days and after 12 months will be derived from the Kaplan-Meier estimators with 95% confidence limits.

Additional details of the statistical analysis will be specified in the statistical analysis plan of the trial.

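### Investigator withdrawal for violations, non-compliance or relocation may lose 12-month outcomes that a telephone call could still obtain

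*Protocol article*

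**What the plan says.** All references are to the protocol article.

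- **Withdrawal.** Section {11b} opens with the patient's own right: "Subjects may withdraw from the trial at any time at their own request without stating the reason(s) for withdrawal". It then adds that "subjects may also be withdrawn at any time at the discretion of the investigator for safety, behavioral, or administrative reasons". The examples include lack of compliance, significant protocol violations and logistical reasons, the last illustrated by "subject changes his/her doctor or hospital or moves to another location".
- **Intervention.** Under Experimental group, "pDC has to be performed within 24h after ictus", with a minimum size of 12 cm. On adherence strategies, {11c} says "Not applicable, as interventions are performed early after poor-grade SAH while patients are unconscious".
- **Endpoint.** Trial design {8} describes "blinded ratings with regard to the mRS assessment during telephone interviews". The schedule in {13} has the mRS by telephone interview at 12 months (visit 9) and 24 months (visit 10).
- **Blinding.** Under {17a} allocation is open and only the mRS raters are blinded.
- **Missing outcomes.** For the primary analysis, {20a} states that "the outcome of all patients with missing data for the primary outcome at 12 months will be counted as unfavorable". The last sentence of {20c} repeats this. The first paragraph of {20c} instead prescribes multiple imputation of the mRS and makes the unfavorable coding a sensitivity analysis.
- **Retention.** Under {18b}, contact data "for each participant and their next of kin (if allowed) will be obtained after recruitment to ensure complete follow-up".

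**The concern.** The three grounds look like general wording that does not suit this design. The experimental procedure is over within a day, so withdrawing a patient later for non-compliance or a violation has little to act on except follow-up. A patient who moves or changes hospital can still be telephoned.

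The person who decides on withdrawal knows the arm. The 24 h and 12 cm requirements exist only in the pDC arm, so violations of them can arise only there. If withdrawal means that the 12-month call is not made, an obtainable outcome goes missing, possibly more often in one arm. Under {20a} a survivor with mRS 0–4 would then be scored as a failure. Excess loss in the pDC arm would hide a benefit, and excess loss in the control arm would inflate or create one. No later analysis can recover an outcome that was never collected.

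**Working it through.** **Inputs.** From Sample size {14}: 30% vs 50% favorable, 102 per group, 80% power, simulations with at least six centers, 216 patients in total. From {20a}: two-sided Mantel-Haenszel test at 5%, stratified by center. From {9}: 9 centers. From {16a}: 1:1 allocation. The article states no dropout rate. The implied allowance is 216 − 2 × 102 = 12 patients, or 12/216 = 5.6%.

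**Test.** In center k, let n1 and n0 be the arm sizes, N = n1 + n0, a the favorable outcomes under pDC and t the favorable outcomes in both arms. Then E = t·n1/N and V = n1·n0·t·(N − t) / [N²(N − 1)]. The test rejects if (|Σ(a − E)| − c)² / ΣV > 3.84, with c = 0.5 (corrected) or c = 0 (uncorrected). The article does not say which is used, so both are shown.

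**The plan's own figure.** With 102 per group and six equal centers, simulated power is 80% corrected and 84% uncorrected; nine centers give the same. The stated 80% is reproduced with the correction, so the sample size itself is not at fault.

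**Effect of lost outcomes.** If a fraction m of an arm is lost and scored unfavorable, and the lost patients have the same true favorable rate p as the rest of that arm, the scored rate is p(1 − m). With 108 per arm and nine equal centers:

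| Loss (assumed) | pDC rate | Control rate | Difference (points) | Power, corrected / uncorrected |
|---|---|---|---|---|
| None | 50% | 30% | 20.0 | 82 / 85% |
| 12 patients, 6 per arm | 47.2% | 28.3% | 18.9 | 78 / 82% |
| 5%, pDC only | 47.5% | 30% | 17.5 | 71 / 75% |
| 10%, pDC only | 45% | 30% | 15.0 | 57 / 63% |
| 12 patients, pDC only | 44.4% | 30% | 14.4 | 54 / 60% |
| 12 patients, control only | 50% | 26.7% | 23.3 | 93 / 95% |

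Example, 12 lost from pDC: m = 12/108 = 0.111; 0.50 × (1 − 0.111) = 0.444; 0.444 − 0.300 = 0.144.

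**No true effect, 12 lost in one arm only.**

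- Both true rates 30%: spurious difference 0.30 × 0.111 = 3.3 points; two-sided rejection about 6 / 8%.
- Both true rates 50%: spurious difference 0.50 × 0.111 = 5.6 points; two-sided rejection about 10 / 13%.
- With no loss, the test rejects in about 3.5 / 5%.

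**Dependence on who is lost.** If none of the 12 would have had a favorable outcome, the shift is zero. If all 12 would have, it is 12/108 = 11.1 points. The table lies between these two.

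**The case against.** The strongest reply is that the harmful step is not written down. Section {11b} says patients may be withdrawn; it does not say that the 12-month call is then dropped. This is a condensed article, and procedures after withdrawal may stand in the full protocol. That holds, and it is why the point says may. Even so, the section's first sentence concerns leaving the trial, and nothing shown limits the next paragraph to study procedures.

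Several stronger readings are tempting but not supported:

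- **Withdrawn patients drop out of the intention-to-treat analysis.** Section {22} describes that population as all randomised patients, and both missing-data rules give each of them a value. The risk is missing outcomes, not removal from the analysis set.
- **Every withdrawal becomes a failure.** That follows from {20a} and the last sentence of {20c}, but the first paragraph of {20c} would impute. Imputation avoids the failure-coding bias in this form. The avoidable loss of information remains, and imputation would rest on assumptions about patients whom an unblinded investigator selected.
- **The loss will differ by arm.** The open design and the pDC-only requirements make this plausible. Nothing says that such violations lead to withdrawal, and the direction is unknown. A decompression in a control patient is not clearly a violation, because secondary craniectomy is allowed there.
- **Section {18b} contradicts {11b}.** Collecting contact data and permitting withdrawal can coexist. The two are in tension only.
- **Many survivors would be withdrawn because they change facility.** The article gives no figure on transfers, and the point does not need one.

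It is also fair that evenly spread loss does little harm: power falls from 82% to 78%.

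**Conclusion.** The point holds as a risk that the stated rule creates, not as a demonstrated bias. Three of the listed grounds do not stand in the way of the primary endpoint, yet they permit withdrawal by someone who knows the arm, and nothing shown preserves follow-up afterwards.

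Under the unfavorable coding, the 12-patient allowance costs about 4 points of power if lost evenly. If it falls in one arm, power ranges from 54% to 93% (corrected test), and with no true effect the two-sided rejection rate is about 6–10% corrected or 8–13% uncorrected. These sizes rest on assumed loss rates, equal centers, and losses unrelated to outcome within an arm. They do not apply if the imputation rule governs the primary analysis. The change should be made because it removes the risk at very little cost.

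**What to change.** In {11b}, separate stopping a study procedure from leaving follow-up:

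- Delete significant protocol violations, lack of compliance, and change of doctor, hospital or residence as grounds for withdrawal from the trial.
- Handle violations through the per-protocol population that {20a} already plans.
- State that vital status and the telephone mRS are collected at 12 and 24 months for every randomised patient unless the patient or legal representative withdraws consent to data collection.

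Separately, {20a} and {20c} should name one primary rule for missing outcomes, since the size of this problem depends on it.

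The cost is an amendment to the protocol and consent wording. The telephone interviews are already in the {13} schedule for all patients.

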### Strategies to improve adherence to interventions {11c}

Not applicable, as interventions are performed early after poor-grade SAH while patients are unconscious.

### Relevant concomitant care permitted or prohibited during the trial {11d}

There are no specific treatments that are prohibited during the trial. All patients receive standard SAH therapy.

### Provisions for post-trial care {30}

Every subject participating in the trial is insured against any trial-related illness/injuries pursuant to the legal requirements, which may occur during the trial.

The investigator will inform the subject of the existence of the insurance, including the obligations arising from it.

### Outcomes {12}

#### Primary outcome

Comparison of the combination of mortality and severe disability between study arms, assessed by mRS between both study arms 12 months after the subarachnoid hemorrhage, dichotomized in “favourable” (mRS 0–4) and “unfavourable” (mRS 5–6) outcome.

#### Secondary outcome

a) Analysis of mortality at 7 and 90 days and at 12 monthsb) Comparison of date of death in patients with pDC vs. no pDC after SAHa) Comparison of length of ICU -stay in patients with pDC vs. no pDC after SAHb) Comparison of length of hospital stay in patients with pDC vs. no pDC after SAHEvaluation of the rate of secondary DC due to intractably raised ICPEvaluation of the use of duraplasty after craniectomyEvaluation of the correlation between size of craniectomy and clinical outcomeRate of complications due to craniectomy assessed by AEs/SAEsAnalysis of mRS in patients with pDC vs. no pDC before SAH and 10–14 days, 30 days, 90 days, 180 days, and 2 years (long-term follow-up) after SAHAnalysis of SF36 scores and EQ-5D scores in patients with pDC vs. no pDC 12 months after SAH

### Participant timeline {13}

**Table Tabb:** 

	Visit 1 Screening	Visit 2	Visit 3	Visit 4	Visit 5	Visit 6	Visit 7	Visit 8	Visit 9 End of study (EOS)	Visit 10 Long-term FU
Visit window		Max. 24h after SAH	24h after the aneurysm repair	10–14d	End of ICU therapy	30d ± 7d	90d ± 14d	180d ± 14d	12mo ± 30d	24mo ± 30d
Informed consent	√									
Including/excluding criteria	√									
Demographic data	√									
Medical history/anamnesis	√									
CCT or MRI	√		√	√			√			
Vital signs	√		√	√						
Randomization	√									
Decompressive craniectomy		√								
Best medical treatment	√	√	√	√	√	√				
Details of ICU therapy^3^/length of hospital stay					√				√	
Replacement of bone flap							√			
Physical examination^1^	√			√		√	√		√	
mRS assessment in the clinic	√^4^			√		√^2^	√^2^			
Telephone interview incl. mRS^2^						√	√	√	√	√
Documentation of routine laboratory^5^	√			√						
QoL questionnaires (SF36 and EQ-5D)									√	
AEs/SAEs		√	√	√		√	√	√		

^1^Physical examination in visits 7 and 9 only if reasonable for the patient

^2^mRS score to be assessed at the clinic if the patient and next of kin attend visit 6 and visit 7; otherwise, the score is assessed by a telephone interview

^3^Details of ICU therapy: days of ICU therapy/days of sedation/days of hypertension therapy for vasospasm therapy/days of increased ICP (ICP > 15)

^4^mRS score before SAH

^5^Gamma-GT, hemoglobin, Quick, creatinine, leukocytes, c-reactive protein (according to local clinical routine)

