### Sample size {14}

The sample size/power calculation is based on a retrospective single-center study and literature review [14].

In this single-center study, 38 patients received pDC and 49 received the best medical treatment, whereas 14 of them underwent secondary DC due to intractably elevated ICP. After 2 years, 10 out of 38 (26%) patients who underwent pDC achieved a favourable outcome compared with 10 out of 49 (20%) patients in the control group (*p*=0.61). In a systematic review of the literature and after selection, 64 out of 131 patients who underwent pDC (49%) achieved a favourable functional long-term outcome.

Simulation analyses showed that the planned Mantel-Hanzel test will have a power of 80% to detect an improvement of the rate of patients with the favorable outcome from 30% under the control intervention to 50% under pDC if the sample size is 102 patients per group. The simulations were performed, assuming minimum six centers. To account for the loss of information due to possible dropouts, 216 patients will be included in the study.

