### Composition of the data monitoring committee, its role, and reporting structure {21a}

The Data Safety Monitoring Board (DSMB) is an independent committee monitoring the study progress of the safety of trial participants and the quality of the collected data (by monitoring reports) and should make recommendations on the discontinuation, modification, or continuation of the trial. The tasks of the DSMB in the trial are the following:

The DMSB will review all SAEs of all patients so far recruited to the trial regularly.

The coordinating investigator can ask the DSMB at any time to review any data from the trial and to decide whether to proceed with the trial without changes, to modify the trial, or to stop the trial entirely. The data provided to the DSMB for review may also include so far unmonitored data.

The DMSB is free to suggest any modifications regarding the trial (e.g., stopping of the trial, modifications of the protocol).

The DSMB will include at least 3 members with experience in the conduct of the study and individual expertise in the field of neurology and biometrics. Further details concerning members, function, reports, and modalities of meetings are provided by the DSMB Charter of this trial.

The Data Safety Monitoring Board (DSMB) has been appointed to review the conduct and results of this trial at 2 enrolment landmarks (after 50 and 100 of the patients have been enrolled). The DSMB is charged with reviewing safety data in both arms of the trial. The DSMB will be empowered to stop the study for evidence of harm but not for evidence of lack of efficacy. The DSMB is also asked to offer perspective on any therapeutic or diagnostic testing advances that may occur during the course of the trial that may influence the outcome. If protocol modifications are warranted, close consultation among the DSMB, the SZB staff, and the study leadership will be required. Further details are provided in a separate DSMB charter.

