### Adverse event reporting and harms {22}

Any AE defined in the trial protocol as relevant for the evaluation and analysis of the clinical trial has to be documented in the CRF on the respective adverse event report form. The following criteria will be assessed: type, beginning, end, and outcome of the event (recovered, improved, unchanged, recovered with sequelae, worsened death, unknown). Pregnancy is not an exclusion criterion in this lifesaving treatment study.

All safety evaluations will be performed on the ITT population, which consists of all patients who were randomized. Frequency tables and/or summary statistics will be provided as described below for the observed adverse events (AEs) and for patients having a respective AE:Per system organ classesPer preferred termsTherapy-related AEsSerious AEs related to therapy

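### Scheduled AE/SAE collection stops at about day 180, so craniectomy complications between then and the 12-month end of study have no planned capture

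*Protocol article*

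**What the plan says.** In the schedule table of the protocol article (Participant timeline {13}), the AEs/SAEs row is ticked at Visits 2, 3, 4, 6, 7 and 8. It is blank at Visit 9 (12 months, labelled end of study) and at Visit 10 (24 months). The row "Replacement of bone flap" has a single tick, at Visit 7.

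Outcomes {12} lists the rate of craniectomy complications as a secondary outcome, names AEs/SAEs as its source, and gives no period. Other outcomes do have dates: mRS for the primary endpoint at 12 months, SF36 and EQ-5D at 12 months, and, under Statistical methods {20a}, "Mortality after 7 and 90 days and after 12 months will be derived from the Kaplan-Meier estimators".

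On exposure to craniectomy, the Experimental group section states: "All patients in the study arm will undergo a pDC of at least 12 cm". Controls may have a secondary DC only as a last resort.

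On safety reporting, Adverse event reporting and harms {22} says: "Any AE defined in the trial protocol as relevant for the evaluation and analysis of the clinical trial has to be documented in the CRF". It also says: "All safety evaluations will be performed on the ITT population, which consists of all patients who were randomized". Neither sentence sets an end date for AE recording or extends it beyond Visit 8. For the monitoring board, section {21a} says: "The DMSB will review all SAEs of all patients so far recruited to the trial regularly".

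**The concern.** A craniectomy usually leads to a second operation to replace the bone flap, and the plan schedules that operation at about three months. The only stated source for the complication outcome closes about three months later, half-way to the trial's own end-of-study visit. If a replacement slips past Visit 8, the table provides neither an entry for the operation nor a later AE visit.

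Two things are at stake. First, benefit is measured at 12 months and harm to about six, so the two sides of the balance cover different periods. Second, exposure to this harm differs between the arms by design. Late events that go unrecorded would come mostly from the pDC arm, which tends to flatter pDC in any between-arm safety comparison.

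The primary endpoint does not fill the gap. It counts mRS 0 to 4 as favourable, so a late complication in a patient who stays at mRS 4 or better leaves it unchanged. A death after day 180 counts for mortality, but no scheduled SAE visit follows it to show whether it was preceded by a craniectomy or flap complication.

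**Working it through.** The plan gives no figure for this point, so the check is a reading of the grid followed by interval arithmetic.

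**1. Inputs from the schedule table** (12 months taken as 365 days)
- Visit 7, flap replacement: 90 ± 14 days, so day 76 to 104.
- Visit 8, last AE/SAE tick: 180 ± 14 days, so day 166 to 194.
- Visit 9, end of study: 365 ± 30 days, so day 335 to 395.

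**2. Scheduled AE follow-up after an on-schedule replacement** (Visit 8 minus Visit 7)
- Nominal: 180 − 90 = 90 days.
- Shortest: 166 − 104 = 62 days.
- Longest: 194 − 76 = 118 days.

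**3. The same if AEs/SAEs were also collected at Visit 9**
- Nominal: 365 − 90 = 275 days.
- Shortest: 335 − 104 = 231 days.
- Longest: 395 − 76 = 319 days.

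**4. Period with no scheduled AE/SAE capture before end of study** (Visit 9 minus Visit 8)
- Nominal: 365 − 180 = 185 days.
- Shortest: 335 − 194 = 141 days.
- Longest: 395 − 166 = 229 days.
- Share of the 12 months that is covered: 180/365 = 49%.

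**5. Where craniectomies fall by arm.** With equal arms, every pDC patient operated on, and a fraction q of controls having a secondary DC, the pDC share of craniectomies is 1/(1 + q). The only figure in the article for q is the retrospective series under Sample size {14}: "49 received the best medical treatment, whereas 14 of them underwent secondary DC due to intractably elevated ICP". That gives q = 14/49 = 29%, used here as an assumption with a range.

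| q in controls | pDC share of craniectomies |
|---|---|
| 10% | 1/1.10 = 91% |
| 29% (14/49) | 1/1.286 = 78% |
| 50% | 1/1.50 = 67% |

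These shares are before deaths. Patients who die before flap replacement never carry its risk, so the table gives the direction of the imbalance and not a count of patients at late risk.

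**6. What cannot be computed.** The number of missed events needs the number of survivors with a craniectomy in each arm, the proportion of replacements done after Visit 8, and the rate of complications arising after Visit 8. The article gives none of these.

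**The case against.** **No contradiction in the text.** The complication outcome has no stated window, so stopping at 180 days breaches nothing, and nowhere does the article claim 12-month safety. This is correct: the point is a poorly fixed design choice. The missing window is part of the problem, because a reader will set the rate beside 12-month efficacy.

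**The article condenses a fuller protocol.** AE definitions are left to it, and the reporting period may be too. That stands as a caution. But the table is an explicit schedule, and nothing shown extends it. If the full protocol collects AEs for longer, the published table misstates it and needs correcting anyway.

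**The outcome is a rate, not a comparison.** Within craniectomy patients, primary and secondary DC are followed on the same visit schedule. This is fair, and it limits the differential effect to between-arm comparisons, such as AE tables on all randomised patients. Controls with a secondary DC are affected too, so the imbalance is relative. The article also does not say whether a flap-replacement complication counts as one due to craniectomy.

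**Late harm is not invisible.** Visit 9 has a telephone interview with mRS, a physical examination where reasonable, quality-of-life questionnaires and an entry for hospital stay. Harm that leads to death or mRS 5 enters the primary endpoint. This stands, but none of these entries records a complication as such.

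**Stronger readings that the article does not support.** A reader might infer that pDC will be shown as safer than it is by a known amount, or that 108 pDC patients against about 31 controls (14/49 × 108 = 30.9) carry the late risk. Those counts ignore deaths in a disease that the article describes as having high mortality; planning assumes 50% (pDC) and 70% (control) with mRS 5 to 6, which includes death. Any figure for the proportion of late replacements has no source in the article. A reader might also infer that the monitoring board can never see late events. A site may report one unprompted, and the coordinating investigator may ask the board to review any trial data at any time. What is missing is scheduled capture.

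**Conclusion.** The point holds as a gap in scheduled safety capture. AE/SAE collection ends at day 166 to 194, 141 to 229 days before the end-of-study visit (185 nominal). An on-schedule flap replacement has 62 to 118 days of scheduled AE follow-up, which covers the early postoperative period but not later events, and a replacement after Visit 8 has none. Any resulting loss falls mainly on the pDC arm in a between-arm safety comparison: about 78% of craniectomies would be there if the 14/49 rate applied (67% to 91% for control rates of 50% to 10%), before deaths.

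The size of the undercount cannot be derived, and the article does not show that it is large. The primary test is unaffected. The conclusion assumes that the published table is the operative schedule and that sites collect AEs at the ticked visits.

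**What to change.** - In the schedule table, tick AEs/SAEs at Visit 9, at least for SAEs and for complications of craniectomy or bone-flap replacement, asked retrospectively for the period since Visit 8.
- Allow the date of flap replacement to be recorded whenever it occurs up to Visit 9. This changes data capture only, not the timing of any operation.
- State the time window of the complication outcome, and whether complications of flap replacement count.
- For patients already past Visit 9, recover events from hospital records. If that is not feasible, report the rate as limited to 180 days, so that patients enrolled early and late are not ascertained over different periods.

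Cost: no new patient contact is needed, since Visit 9 already takes place. There will be somewhat more AE/SAE reporting, some record retrieval because recruitment began in October 2019, and a complication rate that may look less favourable. The change may count as substantial under the amendment rules in section {25} and then need a new ethics opinion.
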